### Co-primary outcome measurements

#### Peak VO_2_

The CPX test will be performed at baseline and at the 12th week according to the guidelines [31]. Technicians and physicians performing the tests will be blinded to the study group. Participants will perform a symptom-limited exercise test using a bicycle ramp protocol (10 W/min) to determine peak VO_2_. Testing will be done on an electronically calibrated upright bicycle, with expired gas analysis under continuous electrocardiographic monitoring. Blood pressure will be taken at 3-min intervals and just prior to starting/stopping exercise. Participants will be encouraged to exercise until exhaustion. Perceived exertion will be measured using the 6–20 Borg Scale. Respiratory gas analysis will be performed on a breath-by-breath basis using a metabolic cart (Cardiovit CS-200 Touch, SCHILLER, Baar, Switzerland). The peak VO_2_ will be defined as the highest value for or the plateau of oxygen uptake.

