#### Disease-specific quality of life

The disease-specific quality of life will be self-assessed by the MLHFQ at baseline, the 4th week, 8th week, and 12th week. This validation instrument will consist of 21 items rated on 6-point Likert scales, representing different degrees of impact of CHF on quality of life, from 0 (none) to 5 (very much). It will provide a total score (range 0–105, with a lower number denoting better quality of life), as well as scores for two dimensions, physical (eight items, range 0–40) and emotional (five items, range 0–25). Prior studies have reported that a score of 7 indicates some degree of impaired quality of life, and that an improvement of 5 points represents a clinically significant change [33]. A validated Chinese version of the MLHFQ will be employed in this trial [32].

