### Statistical methods

#### Sample size calculation

Sample size calculation will be based on the co-primary outcomes of the RCT. A sample of 78 patients per group will provide 80% power to detect the difference in both peak VO_2_ = 1.5 (mL/kg/min) and MLHFQ total score = 10 points between groups at a two-tailed significance level of 5%. This accounts for the standard deviation of peak VO_2_ = 3 mL/kg/min and MLHFQ score = 20 points and meets clinically important difference (peak VO_2_ = 1 mL/kg/min [46] and MLHFQ score = 5 points [33]). This would require 156 participants, inflated to 200 to account for the loss to follow-up of approximately 20% of participants. Because each primary endpoint can characterize a clinically meaningful benefit of the intervention on its own, we will use the “or decision rule,” meaning that the study will be regarded as successful if one of the two primary endpoints improves significantly in the intervention group.

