### Quantitative data analysis

Statistical analysis will be performed in a blinded manner by qualified statisticians using PASW Statistics 18.0 (IBM SPSS Inc., Armonk, New York, USA), SAS 9.2 (SAS Institute Inc., Cary, USA), and Stata (Version 13.0, StataCorp). The level of significance will be set at *p* < 0.05. Baseline variables will be reported by groups, descriptively. For the outcome variables, continuous data will be summarized as mean and standard deviation or range, or as median and interquartile range, and categorical data as counts and percentages. The primary analyses for primary and secondary outcome variables will be based on the intention-to-treat population approach, using data collected at baseline and at the 12th week. Differences in terms of outcomes between groups will be compared using an independent *t* test/Mann-Whitney *U* test, as appropriate. For the two co-primary outcomes, the significance level will be Bonferroni-corrected (*α* = 0.05/2 = 0.025). The effect of intervention on outcomes will also be analyzed using multivariate statistical models, with adjustments for baseline score of the outcome variable (where applicable), as well as gender, age, co-morbidities and other variables that are of clinical importance. In addition, multiple imputation methods will be used as a sensitivity analysis to address the issue of missing data. Subgroup analysis will be performed according to gender, cardiac functional classification, left ventricular ejection fraction classifications, and other variables of clinical importance. The secondary analyses for outcome variables will be undertaken as repeated measure analysis and mixed-effects models using all assessment points (4, 8 and 12 weeks). Sensitivity analysis will be performed, including, but not limited to, the analysis for outcome variables using a per-protocol population. Safety will be evaluated by tabulations of AEs, and will be presented with descriptive statistics for each group. A chi-square test or a Fisher’s exact test will be used to compare the frequency difference in AEs between the two groups. To explore potential factors which might influence adherence, a logistic regression model and a linear mixed-effects model will be used and adjusted for potential confounders. Adherence-related data will be taken from exercise log records.

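### The primary test, labelled intention-to-treat, can use only patients with a week-12 value, so the roughly 20% expected to be lost would contribute nothing to it

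*Protocol article*

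**What the plan says.** All of this comes from the protocol article.

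- **Population and time points** (Quantitative data analysis): the primary analyses are "based on the intention-to-treat population approach, using data collected at baseline and at the 12th week".
- **Test** (same section): "Differences in terms of outcomes between groups will be compared using an independent" t test, or a Mann-Whitney test where appropriate. Each co-primary outcome is tested at 0.025.
- **Missing data** (same section): "multiple imputation methods will be used as a sensitivity analysis to address the issue of missing data". No other handling of a missing week-12 value is given for the primary test.
- **Secondary analyses** (same section): "repeated measure analysis and mixed-effects models using all assessment points (4, 8 and 12 weeks"), stated for the outcome variables without restriction.
- **Sample size calculation**: 78 per group, 156 in all, raised to 200 for "loss to follow-up of approximately 20% of participants".
- **Schedules**: quality of life is "self-assessed by the MLHFQ at baseline, the 4th week, 8th week, and 12th week". For peak VO2, "The CPX test will be performed at baseline and at the 12th week" only. The cardiac function and biomarker sections likewise give LVEF, NT-proBNP and hsCRP at baseline and week 12 only.

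**The concern.** The intention-to-treat label promises a comparison of everyone randomised. The chosen test delivers a comparison of those who reach week 12, because the methods that could bring the others in are ranked below it. This follows from what the article states about the order of its analyses, so it is more than a detail awaiting a statistical analysis plan. A plan that follows the article would inherit the ranking.

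Patients are not blinded, MLHFQ is self-reported, and the trial counts as successful if either co-primary outcome is significant. A distorted MLHFQ comparison could therefore decide the trial by itself. For patients who leave after week 4 or week 8, MLHFQ values that bear on their likely course will have been collected, yet the primary test leaves them aside.

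A smaller defect sits in the same section. Models over weeks 4, 8 and 12 cannot be run as described for outcomes with a single follow-up value, and peak VO2, a co-primary outcome, is one of these.

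**Working it through.** **1. The plan's own sample size.** Inputs from Sample size calculation: difference 10 points with SD 20 (MLHFQ), or 1.5 with SD 3 mL/kg/min (peak VO2). Both give a standardised effect of 0.5. Power is 80%, and the per-endpoint alpha of 0.05/2 = 0.025 is from Quantitative data analysis.

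- Normal approximation: n = 2 × (2.241 + 0.842)² / 0.5² = 76.04, so 77 per group.
- t-based solution: 77.3, so 78 per group. The plan's figure is reproduced.
- Inflation: 156 / 0.80 = 195, rounded up to 200. Equivalently, 1 − 156/200 = 22%.

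The stated power thus rests on 78 patients per group with week-12 data. Of the 200 randomised, 20% to 22% (40 to 44) are not expected to enter the test.

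**2. Precision.** At alpha 0.025 and effect 0.5, t-based power is 80% with 78 per group, 81% with 80, and 90% with 100. The last figure is a ceiling, reached only if every randomised patient were fully informative. Imputation or a mixed model recovers part of that gap.

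**3. Bias by arithmetic.** Suppose a share m of one arm is missing, and its mean change is g points worse than that of the arm's completers. The completers' mean is then too favourable by m × g. With m = 0.20 in one arm and no gap in the other:

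| g (assumed) | bias in the group difference |
|---|---|
| 5 | 0.20 × 5 = 1 point |
| 10 | 0.20 × 10 = 2 points |
| 20 | 0.20 × 20 = 4 points |

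If the same share is missing in both arms with the same gap, the two terms cancel and the bias is zero.

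**4. Bias by simulation (MLHFQ).** Assumptions: no true effect; 100 per arm; SD 20 at each visit; correlation 0.7 between visits; 20% missing at week 12 in each arm. Dropout follows a logistic function of the standardised change at week 8, with log-odds of 0.5, 1.0 or 1.5 per SD. The outcome is change from baseline to week 12, tested at 0.025. The SD is the plan's; the correlation and dropout pattern are assumed.

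- Mechanism in the intervention arm only: bias of about 0.7, 1.4 and 1.8 points in favour of the intervention, with type I error of about 3% rising to about 6.5%.
- Control arm only: the same sizes, against the intervention.
- Same mechanism in both arms, or dropout unrelated to outcome: bias about zero and type I error about 2.5%.
- An estimate using baseline, week 4 and week 8 within arm: bias of 0.1 point or less in all of these cases.
- Dropout driven by the unobserved week-12 change, intervention arm only: completers' bias of roughly 1.5 to 3.5 points. The estimate using weeks 4 and 8 is still biased by roughly 1 to 2.5 points.

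By step 3, a bias of 0.7 to 1.8 points corresponds to dropouts faring 0.7/0.20 = 3.5 to 1.8/0.20 = 9 points worse than completers. The article does not say whether SD 20 refers to the score or to its change. If it is the SD of the change, with correlations of 0.5 to 0.7, log-odds of 0.5 to 1.0 and 21% to 24% missing in the affected arm, the bias is 1.1 to 2.9 points and the type I error 3.4% to 8.8%.

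**5. Repeated-measures wording.** The secondary analyses are specified "using all assessment points (4, 8 and 12 weeks") for the outcome variables in general. Peak VO2, LVEF, NT-proBNP and hsCRP have only a week-12 follow-up value, so the sentence cannot be applied to them.

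**The case against.** The article does plan for missing data. It lists multiple imputation, mixed-effects models, baseline-adjusted models and a per-protocol sensitivity analysis, has reasons for withdrawal recorded, and lets a pilot look at retention first. On this view only the ranking is in dispute, and how missing values enter the primary test could be left to the statistical analysis plan. Part of this stands: the article nowhere says that patients without a week-12 value are excluded, so the completers' reading is an inference. It is a strong one. The named test needs the value, the only named remedy is assigned to sensitivity, and the sample size already removes these patients.

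Several stronger readings are tempting, and the documents do not support them:

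- **That the MLHFQ values at weeks 4 and 8 are unused.** They enter the secondary models. They are unused in the primary test only.
- **That the completers' test favours the intervention.** It does so only if outcome-related dropout is concentrated in that arm. The 20% is a sample-size allowance and says nothing about which patients leave. Stopping the exercise is also not the same as missing the visit, since all participants are asked to attend every assessment.
- **That the model-based analysis removes the bias.** It does so under missing at random. The last simulated case shows that it falls short otherwise.
- **That the same figures hold for peak VO2.** With no interim peak VO2 values, the simulation does not speak to it.

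**Conclusion.** The point holds as a recommended change to the ranking of analyses. As written, the primary test would be a complete-case comparison under an intention-to-treat label, with about 20% of randomised patients contributing nothing. The certain cost is precision: power near 80% against a ceiling of 90%. The possible cost for MLHFQ, if dropout tracks worsening in one arm, is a bias of about 0.7 to 1.8 points in either direction. That compares with the 5-point clinically important difference and the 10-point planned difference. Type I error would be about 3% to 6.5% against the nominal 2.5%. These sizes rest on the assumed dropout pattern, the assumed correlation of 0.7 and SD 20 applied to the score. No size is claimed for peak VO2.

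**What to change.** - **MLHFQ:** make the likelihood-based repeated-measures model the primary analysis in all randomised patients, with baseline as covariate and the week-12 treatment contrast as the test. The article already plans a model of this kind as secondary.
- **Peak VO2:** make multiple imputation primary, using baseline and auxiliary variables such as 6MWT and MLHFQ at weeks 4 and 8, followed by a baseline-adjusted comparison.
- **Completers' t or Mann-Whitney test:** move it to sensitivity analysis.
- **Departures from missing at random:** add a delta-adjusted sensitivity analysis for both co-primary outcomes, since both new primary methods assume missing at random.
- **Wording:** limit the repeated-measures sentence to outcomes actually measured at weeks 4 and 8.

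The cost is protocol and analysis-plan wording and some programming. No visit or measurement is added. The downside is that the primary result then relies on a missing-at-random model, and for peak VO2 the auxiliary variables recover only part of the lost information.

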### Qualitative data analysis

For qualitative data, content analysis based on an inductive approach will be conducted and assisted by NVivo v11. Categories and themes will be identified inductively. Analysis will be conducted by three researchers (RA, RB, RC) in three steps. In the first step, RA and RB have independently created two coding structures by reading three to four of the transcribed interviews and extracting meaningful units from the text; RA and RB will then meet to compare the coding structures, discuss differences and agree on a final version. Preliminary findings will be discussed with RC, and feedback will be incorporated into the coding structure. RA and RB will then apply the final coding structure to all transcripts. In the second step, categories will be created from the codes. The structure of the categories will be discussed among the research team. In the final step, categories with similar content will be grouped together into themes. To ensure the reliability of the findings: (1) the interviews will be read repeatedly to obtain an overall understanding of the project, and there will also be a constant comparison between the parts of the analysis and the full text of the interview and (2) awareness of preconceptions will be emphasized throughout the study.

### Trial management and quality control

The management structure is comprised of principle investigators (PIs) including [name], [name], and [name], a Trial Management Group, a Data Monitoring Committee, and a Trial Steering Committee.

The Trial Management Group is responsible for the day-to-day delivery and for conducting the trial. It will be comprised of a project manager as well as a cardiac rehabilitation team and investigators from the GPHCM. The Trial Management Group will meet weekly to discuss trial progress. The project manager will have a face-to face meeting with the PIs every other week.

The role of the Data Monitoring Committee is to review safety and efficacy data and to make recommendations to the Trial Steering Committee. It will be comprised of four fully independent members: one chairman, one senior biostatistician, one cardiologist, and one *Baduanjin* expert from the GPHCM. The Data Monitoring Committee will meet once, prior to the start of patient recruitment, and at least once a year for those years in which patients are involved in exercise sessions.

The responsibilities of the Trial Steering Committee are to approve the main study protocol and any amendments, to monitor and supervise the trial, steering it towards its specific and overall objectives, to review relevant information from other sources, to approve and comment on project deliverables, to consider the recommendations of the Data Monitoring Committee, and to resolve any problems brought up by the Trial Management Group. It will be comprised of one independent chairman, [name], [name], [name], [name], and four other independent members including at least one patient and a public involvement representative. Responsibility for calling and organizing the Trial Steering Committee meetings lies with the PIs. The Trial Steering Committee will meet at least annually, and more frequently as needed. Representatives of the Data Monitoring Committee are to be invited to all Trial Steering Committee meetings.

Before recruitment, the whole research team, including investigators, research assistants, and research nurses will be required to attend a training workshop. This will be done before the trial to ensure their strict adherence to the study protocol and their familiarity with the trial administration process. The data collected in this trial will be comprised of information recorded in CRFs, information on questionnaires, exercise logs, and accelerometers. Data will be entered using the double-entry method. Data quality is to be checked regularly by research assistants and overseen by monitors. Data monitoring will be conducted regularly with standard operation procedures by a team from the GPHCM Key Unit of Methodology in Clinical Research. Inspections will be performed regularly by the GPHCM Department of Science Research. All modifications are to be marked on the CRFs. Data managers will then recheck the data before logging it, and promptly notify the research team if any discrepancies are found. The database will be locked after all data has been cleaned. If participants withdraw from the trial during the study period, the reasons must be documented (if participants are willing) and the rate is to be statistically analyzed.

## Discussion

The EBCR has been recommended in the guidelines for CHF, but it is still in its infancy in China where EBCR services are rare in most regions. The delivery of EBCR should adopt an evidence-based approach, as well as be culturally appropriate and sensitive to individual needs and preferences. The BESMILE-HF study will establish feasibility and provide preliminary evidence on the efficacy and safety of an EBCR program, which will apply *Baduanjin* as the core component in improving exercise capacity and quality of life in patients with CHF. In particular, the BESMILE-HF program has the potential to reach the subgroup of the CHF population with limited physical functional capacity and for whom more intense physical activity is not appropriate.

A limited number of studies have emphasized the importance of individualizing exercise interventions. However, patients’ experience in CHF exercise interventions have not previously been investigated in the Chinese population. This knowledge would help clinicians and researchers in China to gain a context-specific understanding of adherence issues and how standardized interventions could be adjusted to fit individual needs, capacities, and circumstances. Therefore, the BESMILE-HF study will also explore the experience from participants’ perspectives using qualitative research.

Methodological challenges for this study will arise from evaluating a complex intervention as part of EBCR such as (1) training of the whole research team, (2) issues pertaining to the exercise records, and (3) additional physical activity monitoring. Furthermore, due to the nature of intervention, blinding is impossible in this trial. We will make every effort to ensure that outcome assessors, laboratory technicians, data managers, and statisticians are unaware of the treatment allocations.

Altogether, the results of the BESMILE-HF study might provide evidence for how to effectively deliver a contextually adapted EBCR program in China. While this study will lead to conclusions specific to the content, the findings are likely to be relevant for settings with similar lifestyles and demographic profiles, especially those with limited resources.

## Trial status

The pilot study is on-going and its recruitment began in August 2017. Data collection will finish in January 2018. Two main parts, including the RCT and the qualitative component of the BESMILE-HF study will commence in 2018.

## Abbreviations

6MWT: 6-min walking test
AEs: Adverse events
BESMILE-HF: Baduanjin Eight-Silken-Movements wIth SeLf-Efficacy building for Heart Failure
CHF: Chronic heart failure
CPX: Cardiopulmonary exercise test
CRFs: Case Report Forms
EBCR: Exercise-based cardiac rehabilitation
ECG: Electrocardiograph
GPHCM: Guangdong Provincial Hospital of Chinese Medicine
GRC: Global Rating of Change
HADS: Hospital Anxiety and Depression Scale
hsCRP: High-sensitivity C-reactive protein
IPAQ-SC: International Physical Activity Questionnaire short-form Chinese version
MACEs: Major adverse cardiac events
MLHFQ: Minnesota Living with Heart Failure Questionnaire
NT-proBNP: N-terminal B-type natriuretic peptide
PFSDQ-M: Pulmonary Functional Status and Dyspnea Questionnaire- Modified
PIs: Principle investigators
RCTs: Randomized controlled trials
SEE-C: Self-Efficacy for Exercise-Chinese
TUGT: Timed up-and-go test; VO_2_, Oxygen consumption
